### Data monitoring

#### Trial Steering Committee and Data Monitoring Committee

A trial-specific Trial Steering Committee (TSC) and an independent Data Monitoring Committee have been appointed. The CI will report on scientific progress to these committees. Each of these committees will meet at least annually to monitor the progress of the trial and the safety of the trial, respectively.

#### Interim analyses

After the first five cases, a quality assurance analysis will be conducted by the data monitoring group to ensure adequate fhSPECT/SPECT-CT imaging quality for further analysis.

### Harms

#### Assessment and management of risk

Table 4 summarises the risks and mitigations of all interventions above standard care that are to be performed. The definition of adverse events (AEs) is provided in table 5.

**Table 4 T4:** The risks and mitigations of all interventions above standard care

Intervention	Potential risk	Risk management
Radiotracer	Hypersensitivity (patients)	Ask patients about prior reactions to drugs, especially dextran or modified forms of dextran and exclude patients who are allergic. Observe for hypersensitivity signs and symptoms following radiotracer injection. Have resuscitation equipment and trained personnel immediately available.
Radiotracer	Adverse reactions (patients)	The most common adverse reactions (incidence <1%) are injection site irritation and/or pain. We will check for pain and administer analgesics to patients as required.
Radiotracer/SPECT	Radiation exposure (patients)	The effective dose equivalent of radiation exposure to an average dose used in a 70 kg adult is about 0.30 mSV (30 millirem) in males and is about 0.33 mSV (33 millirem) in females. Patients are also exposed to an additional 200 millirem of exposure to CT scan. Therefore, the total radiation exposure per scan is 230 millirem. Some patients (20/150 participants) will undergo two procedures. Therefore, such participants are exposed to an additional 460 millirem because of being involved in the project. The remaining 130/150 participants will be exposed to an additional 230 millirem because of being involved in the project. This is less than the average radiation exposure to a single CT chest. The average radiation exposure per year per individual due to background radiation is about 310 millirem. Therefore, the effective dose equivalent due to participation in the project is about 460/310 years or about 18 months of background radiation. To put this in context, the average radiation in a flight journey of about 1 hour at an altitude of 39 000 ft is about 0.006 mSV (0.6 millirem). Therefore, the dose received is equivalent to 460/0.6=767 hours of air travel.
Radiotracer/fhSPECT	Additional operation time	Total procedure including scanning adds 15–30 min to anaesthetic time. In the case of slow drainage after intraoperative injection, a second scan can be taken 10–15 min after the initial scan. The participants included in the study are those who are fit for major surgery. Therefore, the addition of the 15–30 min of time will not increase the risk significantly.
Sentinel node biopsy	Additional surgical procedure under GA and related wound complications including infection, bleeding, lymph collections	Qualified and trained doctors (surgeons and anaesthetists) will perform the procedure to minimise the risk due to GA and wound complications related to the biopsy.
Radiotracer/SPECT	Radiation exposure (healthcare professionals)	(1) Use waterproof gloves, effective radiation shielding and appropriate safety measures when preparing and handling radiotracer. (2) Radiotracer will be used by or under the control of physicians who are qualified by specific training and experience in the safe use and handling of radionuclides, and who have received approved training. (3) CT scan will be performed by trained healthcare professionals, who are aware of the radiation exposure to CT scan and take adequate precautions to minimise their exposure.

fhSPECT, free-hand single photon emission CT.

**Table 5 T5:** Definitions of AEs

Term	Definition
AE	Any untoward medical occurrence in a patient or study participant, which does not necessarily have a causal relationship with the procedure involved.
Serious AE	Any AE that: Results in death. Is life-threatening.* Requires hospitalisation or prolongation of existing hospitalisation.† Results in persistent or significant disability or incapacity, or consists of a congenital anomaly or birth defect

Hospitalisation for pre-existing conditions, including elective procedures do not constitute an SAE.

* A life-threatening event refers to an incident in which the participant was at risk of death at the time it occurred; it does not refer to a hypothetical situation in which the event might have caused death had it been more severe.

† Hospitalisation is defined as an inpatient admission, regardless of length of stay.

AE, adverse event; SAE, severe adverse event.

The participants are not anticipated to have any unexpected AEs in this trial. The period of observation for events is until the following day of the procedure. AEs and SAEs will be recorded until the end of the period of observation.

It is not required to report expected AEs, and an AE form does not need to be completed for an expected AE. Expected AEs do not need to be reported to the sponsor.

A list of expected AEs includes the following:

Injection site irritation.Pain.Allergy to radiotracer.

If any of these symptoms are accompanied by events consistent with the definition of an SAE as specified in table 5, then the event will be considered an SAE.

National Cancer Imaging Translational Accelerator (NCITA) will be informed of any SAE within 24 hours of the investigator becoming aware. Unexpected, related SAEs should be reported to NCITA within 24 hours of the investigator becoming aware. This will then be escalated to the sponsor.

Local site Research & Development (R&D) protocols for reporting SAEs will also be followed. All SAEs will be followed up until a resolution is reached (ie, recovered, recovering, recovered with sequelae, fatal, not recovered or unknown).

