### Trial design

LOOC is a multicentre prospective non-randomised phase II surgical imaging trial. This trial comprises two stages. Patients with newly diagnosed OPC with cervical metastasis will be considered for recruitment. The patient care pathway is shown in figure 1. The trial duration per participant is 4 weeks, with an estimated total trial duration of 54 months.

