#### Subsequent assessments and procedures

The trial procedures are very safe, but all patients will be screened for adverse reactions following the final scan or the day following SNB and all complications will be reported according to the following protocol.

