#### Recording adverse events

All AEs that occur during the period of observation (which is the next day after the procedure) should be recorded on the AE log. Expected and related events do not need to be reported.

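### Adverse event recording stops the day after the procedure, so sentinel node biopsy wound complications that start later are not systematically recorded and the surgical phase is likely to understate them

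*Protocol article*

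**What the plan says.** All references are to the Protocol article.

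- **Window.** Assessment and management of risk states: "The period of observation for events is until the following day of the procedure". It continues: "AEs and SAEs will be recorded until the end of the period of observation". Recording adverse events repeats the limit: "All AEs that occur during the period of observation (which is the next day after the procedure) should be recorded on the AE log". Subsequent assessments and procedures agrees: "all patients will be screened for adverse reactions following the final scan or the day following SNB".
- **Named risks of SNB.** Table 4 gives: "Additional surgical procedure under GA and related wound complications including infection, bleeding, lymph collections".
- **Schedule.** Table 3 (surgical phase) ends with the examination day, on which nodes are excised. AE reporting is marked for the scanning and examination days only. Table 1 (imaging phase) does have an AE mark in its column for 24 hours after the examination day.
- **Length of participation.** Trial design states: "The trial duration per participant is 4 weeks". No AE collection is tied to that period.
- **SAEs.** Under Assessment and management of risk, SAEs are notified within 24 hours of the investigator becoming aware and followed to resolution. No step is described for finding SAEs that begin after the window.

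**The concern.** The protocol names three wound complications of SNB and then applies to SNB the same next-day cut-off that it uses for a tracer injection and a scan. A bleed in the first hours falls inside that period. A wound infection or lymph collection that declares itself later does not. The most invasive intervention in the trial also has the shorter AE schedule: the imaging phase has a 24-hour AE column and the surgical phase has none.

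The surgical phase is meant to show that surgical staging of the contralateral neck is feasible, and the Introduction says that results should feed quickly into late-phase trials. A complication count that leaves out later events would make the procedure look safer than it is, both to those planning such trials and to the Data Monitoring Committee while this one runs.

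**Working it through.** **1. Do the places agree?**

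| Place | Last point at which AEs are sought after SNB |
|---|---|
| Subsequent assessments and procedures | day after SNB |
| Assessment and management of risk | day after the procedure |
| Recording adverse events | day after the procedure |
| Table 3 | day of SNB (examination day) |
| Trial design | participation of 4 weeks, no AE collection attached |

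The three text passages agree with one another, so the next-day limit is a stated rule and not detail left to a fuller document. Table 3 stops a day short of it. Nothing in the article collects AEs between the day after SNB and the end of the 4 weeks.

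**2. How many patients are exposed?** The Sample size section has 75 patients considered for SNB and expects 20% to 30% to have contralateral sentinel nodes.

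- 75 × 0.20 = 15
- 75 × 0.30 = 22.5, rounded to 23

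The stated 15 to 23 patients reproduces. These are the patients with a neck wound attributable to the trial.

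**3. Direction of the error.** Let p be the true risk of a wound complication per SNB patient and c the share of such events that start by the next day. Expected events are n × p; expected recorded events are n × p × c. Because c cannot exceed 1, the recorded count can fall short of the true count but not exceed it. The share lost is 1 − c.

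**4. Illustration only.** The article gives neither p nor c. Assume p from 5% to 20% and c from 10% to 50%. The chance of recording at least one event is 1 − (1 − p × c)^n.

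| | n = 15 | n = 23 |
|---|---|---|
| Expected events, n × p | 0.75 to 3.0 | 1.15 to 4.6 |
| Expected inside window, n × p × c | 0.08 to 1.5 | 0.12 to 2.3 |
| Chance of recording at least one | 7% to 79% | 11% to 91% |
| Same chance with full capture (c = 1) | 54% to 96% | 69% to 99% |

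For example, with n = 15, p = 5% and c = 10%: 1 − (1 − 0.005)^15 = 7%, against 1 − 0.95^15 = 54% with full capture. Over the assumed range of c the share of events lost is 1 − 0.50 = 50% to 1 − 0.10 = 90%. These ranges show how much the answer depends on onset time; they are not estimates for this trial.

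**The case against.** **Early events are counted.** A reader might infer that the named complications cannot be counted at all. That goes too far. Bleeding, infection or a collection that appears on the day of SNB or the next day is inside the window and should go on the AE log. Wound complications are also absent from the list of expected AEs exempt from reporting. The gap concerns later onset only.

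**Serious late events have other routes.** SAE notification runs from the investigator's awareness, local SAE procedures also apply, and the Confidentiality section makes clinical follow-up information available to the trial team. These make total loss of serious late events less likely. They are passive, however, and the text ends SAE recording with the window. Non-serious late events have no described route.

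**No complication rate is a stated outcome.** This stands. The surgical outcome is the occult metastatic rate, which the window does not affect. A reader might calculate an upper limit for zero recorded events: the exact two-sided 95% limit is 1 − 0.025^(1/n), or 21.8% for n = 15 and 14.8% for n = 23. No such analysis is planned, and that figure reflects the small sample, not the effect of the window, so the point does not rest on it.

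**Tracer reactions.** Allergy to radiotracer is on the expected list, and the text says: "It is not required to report expected AEs, and an AE form does not need to be completed for an expected AE". A reader might infer that non-serious tracer reactions vanish from the data. The article does not support this: Recording adverse events requires all AEs in the window to be logged, a log entry is not the same as a form or report, and a reaction meeting the SAE definition is handled as an SAE.

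**Table 3 may be a slip.** Probably so, since three text passages agree on the next day. Correcting it alone would still leave the window at one day.

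**Conclusion.** The concern holds for later-onset events. As written, wound complications that start after the day following SNB are not systematically sought or recorded, so the surgical phase is likely to understate them in the 15 to 23 patients exposed. That conclusion rests on the text and on one modest assumption: that some of the complications named in Table 4 begin after the next day. The direction is certain once any do; the size cannot be derived, because the article gives no onset times or rates. The 50% to 90% loss follows only from the assumed range of c. The stated primary outcomes are untouched. The change is worth making because the omission weakens the safety information from a phase about surgical feasibility and is cheap to repair.

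**What to change.** 1. For SNB patients, extend AE and SAE recording beyond the next day, for example to the end of the 4-week participation or to the start of definitive treatment if that comes first. Capture the events when the SNB result is discussed with the patient, or from the medical notes.
2. Make wound infection, bleeding and lymph collection solicited events, each with a yes/no answer and an onset date, so that absence is recorded and not presumed.
3. Add the matching column to Table 3, including the next-day check, and align it with Subsequent assessments and procedures, Assessment and management of risk, and Recording adverse events.

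The cost is a protocol amendment and one extra eCRF page for about 15 to 23 patients. No trial procedure is added and clinical management is unchanged. Two limits remain. The article does not say when the SNB result is discussed, so for some patients the notes may be the only source. Late events may also be harder to attribute to SNB once definitive treatment begins, which is the reason for the earlier cut-off suggested in item 1.

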#### Assessments of adverse events

Each AE will be assessed for severity, causality, seriousness and expectedness as described below.

#### Causality

The assessment of the relationship of AEs to the procedure is a clinical decision based on all available information at the time of the completion of the CRF.

The following categories listed in table 6 will be used to define the causality of the AE.

**Table 6 T6:** Categories for causality of the adverse event

Category	Definition
Definitely	There is clear evidence to suggest a causal relationship, and other possible contributing factors can be ruled out.
Probably	There is evidence to suggest a causal relationship, and the influence of other factors is unlikely.
Possibly	There is some evidence to suggest a causal relationship (eg, the event occurred within a reasonable time after administration of the study procedure). However, the influence of other factors may have contributed to the event (eg, the participant’s clinical condition, other concomitant events).
Unlikely	There is little evidence to suggest there is a causal relationship (eg, the event did not occur within a reasonable time after administration of the study procedure). There is another reasonable explanation for the event (eg, the participant’s clinical condition).
Not related	There is no evidence of any causal relationship.
Not assessable	Unable to assess on information available.

#### Expectedness

The expected is defined as shown in table 7.

**Table 7 T7:** Expectedness of adverse event

Category	Definition
Expected	An adverse event that is consistent with the information about the procedure defined in this protocol.
Unexpected	An adverse event that is not consistent with the information about the procedure defined in this protocol.

#### Recording adverse events

All AEs that occur during the period of observation (which is the next day after the procedure) should be recorded on the AE log. Expected and related events do not need to be reported.

#### Recording and reporting serious adverse events

All reportable serious AEs will be recorded in the medical records and the appropriate eCRF and the AE log.

### Auditing

#### Trial Management Group

The trial management group (TMG) will include the CI, the clinical and scientific leads for the trial and the NCITA operational team. The TMG will be responsible for overseeing the trial. The group will meet at least every 6 months during the period of recruitment and annually during the follow-up period and will send updates to PIs. The TMG will review recruitment figures, the ongoing progress of the scientific studies and any resulting necessity for modification of the characteristics of subjects to be recruited to the trial and any consequent requirement for substantial amendments to the protocol prior to submission to the REC. All PIs will be kept informed of substantial amendments. The TMG will additionally submit periodic progress reports to the REC and sponsor.

#### Trial Steering Committee

A trial-specific TSC will be appointed. The CI will report on scientific progress to this committee, which will meet at least annually to monitor both the progress and safety of the trial.

Before any NHS site may be opened to recruit participants, the CI/PI or designee must receive NHS permission in writing from the Trust R&D. It is the responsibility of the CI/PI or designee at each site to ensure that all subsequent amendments gain the necessary approvals, including NHS permission (where required) at the site. This does not affect the individual clinician’s responsibility to take immediate action if deemed necessary to protect the health and interests of individual participants.

An annual progress report (APR) will be submitted to the REC within 30 days of the anniversary date on which the favourable opinion was given, and annually until the trial is declared ended. The CI will prepare the APR. Within 90 days after the end of the trial, the CI/sponsor will ensure that the main REC is notified that the trial has finished. If the trial is terminated prematurely, those reports will be made within 15 days after the end of the trial.

The CI will supply the sponsor with a summary report of the trial, which will then be submitted to the REC within 1 year after the end of the trial.

## Ethics and dissemination

### Research ethics approval

The trial protocol, participant information sheet, consent form, GP letter and other supporting documents have been approved by the Health Research Authority and the Yorkshire & The Humber-South Yorkshire Research Ethics Committee (REC ref: 20/YH/0111). The LOOC trial is registered with ClinicalTrials.gov, ID: NCT04498221.

### Protocol amendments

Protocol modifications will be notified to the competent authority, ethics committee and investigators by the LOOC trial office.

### Consent

Patients who fulfil the eligibility criteria will be provided with a patient information sheet (PIS) by the investigator or a designated appropriately trained member of the research team, who will be present to answer any questions regarding the aims, methods, anticipated benefits and potential hazards of the trial. They will explain that participants are under no obligation to enter the trial and that they can withdraw at any time during the trial, without having to give a reason.

The person taking consent will be suitably qualified and experienced and will have been delegated this duty by the PI on the Staff Signature and Delegation of Tasks log. Potential participants will be offered sufficient time (at least 24 hours) to consider the trial, allowing time for discussion with family/friends/GP. The participant will be given the opportunity to ask questions and to be satisfied with the responses prior to written consent being taken. No trial procedures will be conducted prior to the participant signing the trial consent form. Following consent, the patient will be enrolled in the trial and allocated a unique pseudo-anonymised subject number. A copy of the signed informed consent form will be given to the participant. The original signed form will be retained in the investigator site file and a copy placed in the medical notes. The PIS and consent form will be reviewed and updated if necessary throughout the trial (eg, where new information becomes available) and participants will be re-consented as appropriate.

### Confidentiality

All personal identifiable data collected during the trial will be handled and stored in accordance with the Data Protection Act (2018) and GDPR and all other applicable regulations and legislation. To preserve patient anonymity, only the allocated subject number and subject identifier will be recorded on the CRFs. Medical records (case notes and hospital trust computer databases) may be accessed by the recruiting site for up to 4 years from the date of consent for the purpose of data clarification. Information about participant demographics, medical history and concomitant medication and tumour characteristics, together with clinical follow-up information, will be made available to the trial team.

### Access to data

#### Archiving

UCL and each participating site recognise that there is an obligation to archive trial-related documents at the end of the trial. The CI will archive the trial master file at UCL and the PI at each respective site will locally archive trial documents for 20 years and in line with all relevant legal and statutory requirements.

#### Intellectual property

No background intellectual property rights (including licences) are required and no commercially exploitable intellectual property is likely to be generated during this research.

#### Data sharing statement

Once the initial trial publication has been released, all participant data collected will be de-identified and shared as per the NCITA policy, which allows access via request to the TMG. Once all trial publications (primary, secondary, tertiary) are in the public domain, the data will be open access. The study protocol, statistical analysis plan and informed consent form will also be available through planned open access publication.

#### Ancillary and post-trial care

UCL holds insurance against claims from participants for injury caused by their participation in the trial. Participants may be able to claim compensation if they can prove that UCL has been negligent. However, as this trial is being carried out in a hospital, the hospital continues to have a duty of care to the participant of the trial. University College London does not accept liability for any breach in the hospital’s duty of care, or any negligence on the part of hospital employees. This applies whether the hospital is an NHS Trust or otherwise.

Participants may also be able to claim compensation for injury caused by participation in this trial without the need to prove negligence on the part of UCL or another party. Participants who sustain injury and wish to make a claim for compensation should do so in writing in the first instance to the CI, who will pass the claim to the sponsor’s Insurers, via the sponsor’s office.

Hospitals selected to participate in this trial shall provide negligence insurance cover for harm caused by their employees and a copy of the relevant insurance policy or summary shall be provided to UCL, on request.

